### Statistical considerations

We have funding and plan to enroll and randomize 100 patients. While this number of patients is insufficient to reach a definitive answer about the efficacy of the decision aid and its effect on medication adherence, it is sufficient to ascertain the following differences:

• for knowledge gains, assuming that patients in the control group will be able, on average, to answer 4 of the 9 specific knowledge questions correctly, we will have 92% power to detect a ≥42.5% increase in mean knowledge (to a mean of 5.6 questions answered correctly) in the intervention group, assuming equal variances between the two arms and alpha = 0.05;

• for adherence, estimating that the 6 month adherence rate is 65% (null hypothesis), we will be powered (80%) to detect a difference (alpha = 0.05) in adherence rates of 35% (88% alternative hypothesis). To our knowledge, there is no policy- or patient-important minimum difference in adherence rates identified in the literature to otherwise guide the choice of a threshold.

The distribution of study variables will be described (using frequencies for categorical variables and measures of central tendency for continous variables) and compared using relative (relative risk) or absolute (mean differences) measures of association and their 95% confidence intervals. Because we expect a very low patient-to-clinician ratio, we do not anticipate having to use generalized estimating equations to adjust for clustering by clinician. To test hypotheses of association, we will use Wilcoxon rank-sum tests to compare medians, and Chi-square or Fisher's Exact tests to compare frequencies. All analyses are based on two-sided tests at significance level 0.05. Consistent with the intention to treat principle [39], all efforts will be placed on avoiding missing data and all patients will be analyzed in the arm to which they were randomized; participants with missing data will not be part of the analyses requiring the missing data. All analyses will be conducted using SAS (SAS Institute, Cary, NC).

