### Randomization

A computer-generated allocation sequence will randomize patients 1:1 in a concealed fashion to control (usual care + booklet) or intervention (*OSTEOPOROSIS CHOICE *decision aid). The study coordinator will complete the following steps:

• assess the eligibility of the patient, obtain the patient's written informed consent and enroll the patient;

• access a secure study website, input patient identifiers to document patient eligibility;

• obtain from the website interface the arm of the study to which the patient is allocated;

• when the website is not available, the coordinator will contact the study statistician and a similar procedure will be used to provide concealed random allocation.

After randomization, only data analysts will remain blind to allocation. If a patient were suspected of having incorrectly enrolled, e.g., the patient is found to be ineligible after enrollment and randomization, the study coordinator will present the case to the study principal investigator ([name]) for consideration. Following existing recommendations [30], the principal investigator will decide on exclusion while unaware of any consequences of enrollment, including the patient's allocation or outcomes.

The following issues were considered in our choice[15] to randomize clinics, clinicians, or patients:

• *Randomize by clinics *- This approach would enable us to train everyone in the intervention (and control) clinics to use (or not) the decision aid. Disadvantages included the small number of available clinics, difficulty in balancing the number of participating clinicians and patients across sites, and limited ability to avoid selection bias or implement allocation concealment.

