## Discussion

We have presented the design of a trial to evaluate the effect of a decision aid for bisphosphonate treatment in postmenopausal women receiving primary care (*OSTEOPOROSIS CHOICE*). While this is a feasibility trial for a new decision aid, we also seek to determine if the decision aid can transfer knowledge, and if so, can it improve patient involvement in making decisions about their care, and whether such an improvement will have a discernible effect on adherence. We also discuss the pros and cons of patient randomization vs. cluster randomization, and present a method using video recordings of visits to assess contamination, a key potential outcome of our decision to randomize by patients, rather than clinics or clinicians.

Pursuing adherence as an outcome of decision support technologies is pertinent for clinical policymaking, but it is challenging from a clinical trials design standpoint, especially when few patients take up the medication of interest after the consultation. In this case, the power of a trial to measure differences in this outcome depends not only on the efficacy of the intervention, but also on the proportion of patients at risk of nonadherence. The latter depends on the fraction of patients who leave the consultation with a prescription, a number that could be substantially smaller than the number randomized. Most cohort studies of medication use cannot ascertain the patients who had a discussion about medication use and left the consultation without a prescription. Consequently, the proportion of patients who will begin a new medication is often unknown prior to the study. This pilot study will offer an estimate of the proportion of patients likely to take on bisphosphonates after the study visit, this estimate can inform the size of larger trials of this intervention seeking to evaluate the impact of decision aids on adherence to medication.

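### The 80% power stated for adherence carries no condition, but it needs all 50 women per arm in the comparison; the 35% is a relative increase, and the absolute difference is 23 points

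*Protocol article*

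**What the plan says.** Under Statistical considerations the protocol sets the size by funding: "We have funding and plan to enroll and randomize 100 patients". It concedes that this number cannot settle efficacy or the effect on adherence, but adds that "it is sufficient to ascertain the following differences" and lists two of them. The second is adherence: "estimating that the 6 month adherence rate is 65% (null hypothesis"), after which "we will be powered (80%) to detect a difference (alpha = 0.05) in adherence rates of 35% (88% alternative hypothesis").

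The surrounding terms are:

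- Allocation (Randomization): "A computer-generated allocation sequence will randomize patients 1:1 in a concealed fashion", so 50 women per arm.
- Error rate (Statistical considerations): "All analyses are based on two-sided tests at significance level 0.05".
- Test for proportions (Statistical considerations): "Chi-square or Fisher's Exact tests to compare frequencies".
- Missing data (Statistical considerations): women without the data that an analysis needs are left out of that analysis.
- Entry (Inclusion criteria): only women not on a bisphosphonate or another prescription osteoporosis drug.

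The Discussion says the power to compare adherence rests partly on how many women are at risk of non-adherence. That in turn depends on "the fraction of patients who leave the consultation with a prescription, a number that could be substantially smaller than the number randomized". It adds that this fraction is often not known in advance and that the pilot will estimate it.

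**The concern.** The power statement and the Discussion do not fit together. The first attaches 80% to 100 randomised women without any condition. The second says the number that matters for adherence may be well below the number randomised. A woman who enters untreated and never starts cannot be adherent, so each non-starter either leaves the comparison or counts as non-adherent. The power bullet does not say which, and it allows for neither.

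The effect is also mislabelled. A difference between rates of 65% and 88% is 23 percentage points, not 35.

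At stake is how the adherence result is read. If it is null, a reader who takes the bullet at face value would treat it as evidence, at 80% power, against a 23-point effect. The design may have much less power than that.

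**Working it through.** **Inputs.** From the protocol: 100 women, 1:1, so n = 50 per arm; rates 0.65 and 0.88; two-sided alpha 0.05; chi-square or Fisher's exact test; stated power 80%. Not in the protocol: the fraction of women who start. The fractions below are assumptions, taken as equal in both arms unless stated.

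**Step 1: what the 35% is.** 0.88 / 0.65 = 1.354, a relative increase of about 35% (0.65 × 1.35 = 0.8775, which rounds to 88%). The absolute difference is 0.88 − 0.65 = 0.23. A literal 35-point gap would not give 80%: at 50 per arm, 53% v 88% gives about 98% power, and 65% v 100% gives over 99%. The 35% is therefore relative.

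**Step 2: reproduce the 80% at 50 per arm.**

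- Pooled normal formula: power = Φ[(d − 1.96·√(2p̄(1−p̄)/n)) / √((p₁(1−p₁)+p₂(1−p₂))/n)], with d = 0.23 and p̄ = (0.65 + 0.88)/2 = 0.765. The two standard errors are √(2·0.765·0.235/50) = 0.0848 and √((0.2275+0.1056)/50) = 0.0816. So (0.23 − 1.96·0.0848)/0.0816 = 0.78, and power is 78.3%.
- Arcsine formula: h = 2·arcsin√0.88 − 2·arcsin√0.65 = 0.559; Φ(0.559·√25 − 1.96) = Φ(0.83), giving 79.8%.
- Exact enumeration (binomial probabilities summed over all pairs of counts for which the test rejects): uncorrected chi-square 79.7%, Fisher's exact 72.7%.

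The stated 80% is thus recovered by uncorrected methods with every randomised woman in the comparison. There is no margin for loss: the pooled formula asks for 53 per arm for 80%.

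**Step 3: if 65% and 88% are rates among starters.** The comparison then has n = 50 × start fraction per arm. Exact power for 65% v 88%:

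| Assumed start fraction | n per arm | Chi-square | Fisher's exact |
|---|---|---|---|
| 100% | 50 | 79.7% | 72.7% |
| 90% | 45 | 76% | 66% |
| 70% | 35 | 63% | 53% |
| 50% | 25 | 51% | 36% |
| 40% | 20 | 41% | 29% |
| 30% | 15 | 33% | 18% |

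By the pooled formula, 25 per arm would need about 96% adherence in the intervention arm for 80% power. At 15 per arm, even adherence close to 100% gives only about 73%.

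**Step 4: if 65% and 88% are rates among all randomised women.** Then 50 per arm is the right number. But the rate in all women equals start fraction × adherence among starters, so it cannot exceed the start fraction. At least 65% of controls and 88% of intervention women would have to start.

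Suppose instead that 65% and 88% hold among starters, with non-starters counted as non-adherent. Power then depends on both start fractions:

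- 40% start in both arms: 0.40 × 0.65 = 26% v 0.40 × 0.88 = 35.2%; exact chi-square power 17%.
- 50% start in both arms: 32.5% v 44%; power 22%.
- 40% of controls and 60% of intervention women start: 26% v 52.8%; power about 80%.

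On this denominator, then, low uptake alone does not fix the power. An effect of the aid on starting can restore it.

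**The case against.** The best defence has four parts.

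**The number is not miscalculated.** This stands. The 80% reproduces; the fault lies in an unstated denominator and condition.

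**This is a funding-limited pilot that disclaims a definitive answer, and the Discussion itself raises the prescription fraction and plans to use observed uptake to size later trials.** This stands as mitigation. It makes it less likely that the next trial would be sized on the 80%. But the sentence with the disclaimer goes on to call the number sufficient, and the Discussion does not go back to condition the figure.

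**The planned 95% confidence intervals already serve estimation.** True, and it makes the correction easy. It does not repair the power statement.

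**The case is easily overstated.** This stands too. A reader might infer any of the following, and the protocol supports none of them:

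- *That the 80% holds only if all 100 women start.* This follows only if 65% and 88% are rates among starters, and the protocol does not fix the denominator.
- *That the protocol itself calls full uptake unlikely.* It says the number with a prescription may be substantially smaller and is often unknown.
- *That real power is about 20% to 50%.* That range rests on an assumed 30% to 50% starting, and its lower end needs Fisher's test; chi-square gives 33% at 30% starting.
- *That power is 17% to 22% with all women as denominator.* Those figures assume equal start rates, a weak assumption for an aid whose subject is whether to start.

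**Conclusion.** The concern holds in this form: the 80% is stated without a condition that it needs. It is correct for 65% v 88% when all 50 women per arm contribute and the uncorrected chi-square test is used (79.7%); with Fisher's exact test it is 72.7%. The protocol admits only untreated women, and its own Discussion makes adherence power depend on a fraction it does not know, so the design cannot be relied on to have the stated power.

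The size of the shortfall is conditional. Among starters, power is at best 63% if 70% start and 51% if half start. Those start fractions are assumed, and equal in both arms. With all randomised women as denominator, the two rates need at least 65% and 88% to start, and power then turns on any effect of the aid on starting. The documents do not support a single figure for actual power.

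Separately, and without any assumption, the 35% is a relative increase presented as a difference in rates; the difference is 23 points.

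**What to change.** In Statistical considerations:

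1. State the denominator for the adherence comparison: women who start, or all randomised women with non-starters counted as non-adherent.
2. Restate the bullet along these lines: *80% power (chi-square; 73% with Fisher's exact) for 65% v 88%, a 23-point difference (relative risk 1.35), only if all 50 women per arm contribute to the adherence comparison.*
3. Give power over a range of assumed start fractions, labelled as assumptions. If the denominator is all randomised women, vary the start fraction separately by arm.
4. Either make the sufficiency claim for adherence subject to that condition, or take adherence out of that list and present it as estimation with the 95% confidence intervals already planned.

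The cost is wording only: no extra patients and no change to data collection. The stated power becomes less favourable.

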## Discussion

We have presented the design of a trial to evaluate the effect of a decision aid for bisphosphonate treatment in postmenopausal women receiving primary care (*OSTEOPOROSIS CHOICE*). While this is a feasibility trial for a new decision aid, we also seek to determine if the decision aid can transfer knowledge, and if so, can it improve patient involvement in making decisions about their care, and whether such an improvement will have a discernible effect on adherence. We also discuss the pros and cons of patient randomization vs. cluster randomization, and present a method using video recordings of visits to assess contamination, a key potential outcome of our decision to randomize by patients, rather than clinics or clinicians.

Pursuing adherence as an outcome of decision support technologies is pertinent for clinical policymaking, but it is challenging from a clinical trials design standpoint, especially when few patients take up the medication of interest after the consultation. In this case, the power of a trial to measure differences in this outcome depends not only on the efficacy of the intervention, but also on the proportion of patients at risk of nonadherence. The latter depends on the fraction of patients who leave the consultation with a prescription, a number that could be substantially smaller than the number randomized. Most cohort studies of medication use cannot ascertain the patients who had a discussion about medication use and left the consultation without a prescription. Consequently, the proportion of patients who will begin a new medication is often unknown prior to the study. This pilot study will offer an estimate of the proportion of patients likely to take on bisphosphonates after the study visit, this estimate can inform the size of larger trials of this intervention seeking to evaluate the impact of decision aids on adherence to medication.

An important reason to run feasibility trials of decision aids designed for use in clinical practice is that these tools could directly impact the content and duration of the consultation in favorable or unfavorable ways. When clinicians at multiple sites with different interests and priorities see eligible patients, they may not perceive the need to use the decision aid for this particular decision, may not find it appropriate for use in some patients, and may not use the decision aid appropriately [40]. Thus, an evaluation of the feasibility of the decision aid aided by video recording of as many visits as possible provides a rich database to ascertain these challenges. Results may lead to process modifications in trial design, revised criteria for selection of clinicians and patients, or changes in the decision aid itself, prior to a larger efficacy study. These insights will also affect efforts to implement effective decision aids in practice [41,42].

In conclusion, the *OSTEOPOROSIS CHOICE *trial is designed to provide initial empirical evidence of feasibility and efficacy of a novel approach -- decision aids -- to improve adherence to medication for patients with osteoporosis. We will also seek to assess the feasibility and effect on validity of patient-level randomization as an alternative to cluster randomization at the clinician and clinic level in preliminary studies of decision aid efficacy. The results will inform the design of a larger trial that could provide more precise estimates of the efficacy of the decision aid.

## List of abbreviations

BMD: (bone mineral density); DXA: (dual-energy X-ray absorptiometry); FRAX: (fracture risk assessment tool); WHO: (World Health Organization).
